#### Secondary objectives

To determine the effects that routine use of CMR in non-ischemic HF has on therapeutic decisions on the Composite Clinical Endpoint (CCE), cardiac function, symptoms, quality of life (QoL), and costs. Ancillary measurements will include the safety of imaging tests and adverse reactions to gadolinium contrast agent.

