#### Secondary hypotheses

Routine use of CMR will have a significant impact on treatment decisions, and will (1) lead to more disease specific therapies and/or (2) cause a significant change in the number and class of HF medications, during follow-up. The routine CMR group will also have improved clinical outcomes (CCE), symptoms and QoL and decreased costs compared to the standard of care group during follow-up.

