### Description of interventions (randomized and registry participants)

Baseline: demographic and clinical data will be collected from all participants on standardized case report forms. This data will be collected from the participant and the most recent, routine history and physical examination that have been completed by the treating physician. Quality of life questionnaires (Minnesota Living with Heart Failure (MLHFQ) and EuroQoL Quality of Life Scale (EQ5D)) will be administered. Patients at all sites will undergo standard HF investigations according to published Canadian guidelines [14,36,37]. Each center will have a HF lead, an echo lead and a CMR lead as well as a study co-ordinator.

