### Follow-up

Clinical outcomes will be collected by telephone follow-up, and/or by hospital chart and electronic health record review at three and twelve months and then yearly up to four years, following completion of baseline scans. Data will be recorded on standardized case report forms. Quality of life questionnaires (MLHFQ and EQ5D) will be administered at each follow-up.

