#### Secondary outcomes

For the binary secondary outcomes, such as CCE, referral to HF clinic and HF therapies, chi-square tests will be used to compare the imaging strategies. Logistic regression analysis will be used for adjusting any pertinent baseline differences identified. For continuous secondary outcomes, such as LV function, MLHFQ and EQ5D, analysis of variance will be used to compare trends over time between the imaging strategies. Analysis of covariance will be used for adjusting any pertinent baseline differences identified. For assessing the reproducibility of echo/CMR results, reliability statistics, including intra-class correlations and kappas, will be calculated to compare CMR and echo studies with the core lab interpretations.

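### Quality of life is to be compared by trends, but the hypothesis is a better level during follow-up; a baseline-adjusted mean difference would test it more efficiently

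*Protocol article*

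**What the plan says.** The Secondary outcomes paragraph of the statistical analysis section sets the comparison for the continuous outcomes, with LV function, MLHFQ and EQ5D as examples: "analysis of variance will be used to compare trends over time between the imaging strategies". It continues: "Analysis of covariance will be used for adjusting any pertinent baseline differences identified". The Missing data paragraph adds MMRM for continuous outcomes with several time points, as a way of handling missing values, and names no contrast.

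Under Secondary hypotheses, the prediction for patients assigned to routine imaging is that they "will also have improved clinical outcomes (CCE), symptoms and QoL and decreased costs compared to the standard of care group during follow-up". LV function is not in that sentence. It appears only among the Secondary objectives, in the list "cardiac function, symptoms, quality of life (QoL), and costs", without a direction.

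MLHFQ and EQ5D are collected at baseline (Description of interventions) and again later: "Quality of life questionnaires (MLHFQ and EQ5D) will be administered at each follow-up". Visits fall at 3 and 12 months and then yearly to 4 years, and each patient is followed for 1 to 4 years.

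**The concern.** The hypothesis is about level: is quality of life better in one arm while patients are followed? The stated comparison is about shape: do the two curves change differently? In a repeated-measures analysis of variance, the latter is ordinarily the group-by-time interaction or a difference in slopes.

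The difference matters because routine CMR is a one-off strategy applied at baseline. If it changes diagnosis and treatment, one natural pattern is a shift that is present by month 3 and then persists. An interaction test spreads that single shift over several degrees of freedom. A linear slope fits it poorly. Neither gives the number a reader wants, which is how much better quality of life was. Baseline is a strong predictor of later scores, yet it is to be adjusted for only when the arms are seen to differ. A moderate benefit could therefore go undetected although the data are good enough to show it.

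**Working it through.** **The plan's own figure.** The article gives no power for quality of life. Its only sample size is 252 per arm, for the primary outcome (35% against 50%, 90% power, 10% loss). With the pooled-variance Z-test, two-sided 0.05:

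n = [1.96·√(2·0.425·0.575) + 1.2816·√(0.35·0.65 + 0.50·0.50)]² / 0.15² = 226.2, so 227 evaluable per arm; 226.2/0.9 = 251.3, so 252.

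The figure reproduces and is used below only as the number of patients.

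**Inputs from the article.** 252 per arm; visits at 0, 3, 12, 24, 36 and 48 months; 1 to 4 years of follow-up.

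**Assumptions, not in the article.** Unit SD; compound symmetry with correlation 0.4 to 0.7; last visit at 1, 2, 3 or 4 years in 30, 25, 25 and 20% of patients; a benefit of 0.2 SD from month 3, constant afterwards; two-sided 0.05.

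**Formula.** Let Δ be the vector of arm differences by visit. Its covariance is V = 2·[Σ n_p·Σ_p⁻¹]⁻¹, summed over follow-up patterns p, each with n_p patients per arm and within-patient covariance Σ_p. A contrast C with k rows has noncentrality λ = (CΔ)′(CVC′)⁻¹(CΔ). Power is the chance that a noncentral χ² with k degrees of freedom exceeds its 5% critical value (3.84 for k = 1, 11.07 for k = 5).

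**Worked case, correlation 0.6.**
- Average of the five follow-up differences, baseline difference set to zero by randomisation: SE 0.0595; 0.2/0.0595 = 3.36; power Φ(3.36 − 1.96) = 92%.
- Group-by-time interaction with baseline as a free visit, 5 df: λ = 9.53; power 65%.
- The same 5-df test with the baseline difference set to zero: λ = 13.67; power 83%.
- Slope difference including baseline: 0.0402/0.0253 = 1.59; power Φ(1.59 − 1.96) = 36%.

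**All correlations, power in %.**

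| Comparison | 0.4 | 0.5 | 0.6 | 0.7 |
|---|---|---|---|---|
| Baseline-adjusted average | 86 | 89 | 92 | 96 |
| Interaction, baseline free (5 df) | 46 | 54 | 65 | 80 |
| Interaction, baseline difference zero (5 df) | 76 | 78 | 83 | 90 |
| Slope, baseline included | 26 | 30 | 36 | 45 |
| Average, baseline not used | 77 | 73 | 71 | 68 |
| Interaction, follow-up visits only | 5 | 5 | 5 | 5 |

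**Splitting the gap to the interaction test.** Row 1 minus row 2 is 40, 35, 27 and 16 points. Row 1 minus row 3, the part due to the contrast, is 10, 11, 9 and 6. The remaining 30, 24, 18 and 10 points come from baseline handling.

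**Sensitivity.** With 227 per arm the ranges are 83 to 94% (adjusted average), 41 to 75% (interaction, baseline free) and 24 to 41% (slope). With 227 per arm, complete data, and compound-symmetry or autoregressive correlation of 0.3 to 0.7, they are 88 to 98%, 31 to 79% and 14 to 47%. The ordering does not change.

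**The case against.** **The wording is loose.** The article does not say interaction, slope or parallel curves. A repeated-measures analysis of variance also yields a group effect, and an MMRM can give visit-wise differences. The full analysis plan is not shown and may name a contrast. This stands in part: a trend test is the usual reading but not the only one. Still, the trend comparison is the only target the article states for these outcomes. Neither the conditional covariance adjustment nor the MMRM paragraph replaces it.

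**The test is not blind to an early benefit.** A reader might take the 5% row to mean that a lasting benefit cannot be detected. The article does not support that. For baseline it says "Quality of life questionnaires (Minnesota Living with Heart Failure (MLHFQ) and EuroQoL Quality of Life Scale (EQ5D)) will be administered". With baseline as a visit, a step between baseline and month 3 is itself a departure from parallel curves. Power falls to 5% only if baseline is left out, and nothing in the article says so.

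**Most of the loss is not from the contrast.** This stands, as the split shows. At correlation 0.7 the interaction (80%) even beats an average that ignores baseline (68%). Baseline adjustment is therefore an essential part of the remedy.

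**The assumed shape favours the average.** Therapies are recorded throughout follow-up, so a slowly growing benefit is also plausible. For linear growth to 0.4 SD at 4 years (correlation 0.6, staggered follow-up), the average has 93%, the interaction 88% and the slope 98%. The cost is larger for a smaller slow benefit. With complete data, 227 per arm, growth to 0.2 SD and compound symmetry of 0.3, 0.5 and 0.7, the average has 46, 46 and 56% against 62, 76 and 93% for the slope. This stands as a real trade-off, but a slope answers a different question from the stated hypothesis.

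**Conclusion.** For MLHFQ and EQ5D, the stated comparison does not match the stated hypothesis, and changing it is a cheap improvement. Under the usual trend readings and the assumptions listed, an early lasting benefit of 0.2 SD has 46 to 80% power (interaction, baseline free) or 26 to 45% (slope), against 86 to 96% for the baseline-adjusted average. Only 6 to 11 points of the gap to the interaction test belong to the choice of contrast. The sizes rest on an assumed effect, correlation and follow-up pattern.

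It would go too far to infer that the trial cannot answer its quality-of-life hypothesis: the data are collected, and the planned models can produce the right estimate. Nor does the mismatch extend to LV function, for which no hypothesis of level is stated. The primary analysis and the 252 per group are unaffected.

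**What to change.** In Secondary outcomes, replace the trend comparison for MLHFQ and EQ5D with:

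> For MLHFQ and EQ5D, the between-strategy comparison is the baseline-adjusted difference in mean score, averaged over the scheduled follow-up visits and estimated from the MMRM described under Missing data, with its 95% confidence interval. The baseline score is included whether or not the arms appear to differ on it. The group-by-time interaction is reported descriptively.

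The same estimand can be used for LV function for consistency.

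This costs one short edit, with no new data or patients. The price is lower power than a slope test if benefit accrues slowly: about 5 points in the 0.4 SD case above, more if the eventual benefit is smaller. The choice should be fixed before outcome data are compared by arm.

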### Secondary outcome measures

(i) Treatment effects: at three months and one year, the treating physician will be asked to reassess the HF etiology. The presence of each HF medication class will be re-assessed in addition to the overall number of cardiac medications. The presence of advanced HF therapies will additionally be recorded at each follow-up visit including: implantable device, electrophysiologic study/ablation, cardiac surgery/transplantation, and disease specific therapies (for example, phlebotomy for hemochromatosis; steroids for sarcoidosis).

(ii) Clinical endpoints: Composite Clinical Endpoints (CCE that is, death, cardiovascular (CV) death, HF admission), left ventricular function, QoL, referral to HF clinic, costs and safety will be assessed at three months, then annually for a minimum of one year and a maximum of four years.

Resource utilization and costs: regression methods will be used to assess the incremental costs associated with the routine use of CMR.

(iii) Echo/CMR variability: anonymized copies of CMR and echo studies will be sent to a core lab for interpretation in approximately 10% of cases in order to assess reproducibility and quality assurance of the results. Appendix A.

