#### Primary analysis

For the primary analysis, the definitive diagnosis of cardiomyopathy between routine CMR versus echo with selective CMR, diagnosis will be compared using chi-square techniques. Potential confounding variables of the relationship between the imaging strategies and the primary endpoint will be assessed. In particular, propensity scores based on patient factors (for example, in/outpatient, NYHA class, HF duration, diabetes, atrial fibrillation) and site factors (for example, time-to-imaging, time-to-therapy) will be used in the analysis if necessary to adjust for potential differences. A logistic regression model will be used to assess the occurrence of the endpoints between the imaging strategies (model will include a group indicator variable) adjusting for any pertinent baseline differences identified.

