#### Missing data

‘Missingness’ is considered to be missing at random and mixed methods repeated measures (MMRM) and multiple imputation techniques will be used for handling missing data. In particular, for continuous outcomes at multiple time points MMRM will be used.

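### Two analyses, ANOVA and MMRM, are stated for the repeated continuous secondary outcomes, and baseline adjustment depends on an undefined imbalance trigger

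*Protocol article*

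**What the plan says.** Under Secondary outcomes, the protocol article groups LV function, MLHFQ and EQ5D as continuous outcomes and states that "analysis of variance will be used to compare trends over time between the imaging strategies". The next sentence adds: "Analysis of covariance will be used for adjusting any pertinent baseline differences identified". Under Missing data, after assuming missingness at random and naming MMRM and multiple imputation, it states: "In particular, for continuous outcomes at multiple time points MMRM will be used".

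Both rules reach the same outcomes. At baseline, "Quality of life questionnaires (Minnesota Living with Heart Failure (MLHFQ) and EuroQoL Quality of Life Scale (EQ5D)) will be administered", and the Follow-up section repeats both questionnaires at three and twelve months and then yearly up to four years. LV function is measured on the required baseline echocardiogram and is listed for repeated assessment under Secondary outcome measures.

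The Primary analysis section uses the same conditional language for its logistic model ("adjusting for any pertinent baseline differences identified"). There it follows a named chi-square comparison and a list of example factors. For the continuous outcomes no covariate is named. Analysis populations makes ITT the main population for the secondary objectives.

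**The concern.** There are two separate problems.

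First, ANOVA and MMRM are not interchangeable labels. They can differ in covariance structure, in how incomplete follow-up is handled and in whether the model conditions on baseline. The article does not say that one is a form of the other, or which gives the reported result. Improved quality of life is a stated secondary hypothesis, so the same claim could rest on either analysis.

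Second, adjusting only when an imbalance is noticed misses why one adjusts in a randomised trial. The outcome's own baseline value predicts its follow-up value, and conditioning on it removes that variance however well the arms balance. Waiting for an imbalance gives up that gain in most realisations. Because the trigger is undefined, the decision would be made after the data are seen.

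**Working it through.** **The plan's own figure.** The only size calculation is for the binary primary endpoint: 35% versus 50%, alpha 0.05 (two-sided assumed), power 90%, pooled Z-test.
- n = [1.960·√(2·0.425·0.575) + 1.282·√(0.35·0.65 + 0.50·0.50)]² / 0.15² = 226.2, so 227 per arm.
- Allowing for 10% loss gives 253 (227/0.9) or 250 (227·1.1). The stated 252 is reproduced within rounding.
- With 252·0.9 evaluable per arm, power is 0.90. Nothing below changes this.

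**Inputs for the continuous outcomes.** The article gives no SD, effect or correlation. I assume equal variances at baseline and follow-up, a baseline-to-follow-up correlation rho of 0.3 to 0.7, one follow-up time, and 226 evaluable per arm (252·0.9, rounded down).

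**Variance of the arm difference**, relative to a follow-up-only comparison:
- follow-up only: 1
- change from baseline: 2(1 − rho)
- baseline always in the model: 1 − rho²
- adjusted against change: (1 − rho²) / [2(1 − rho)] = (1 + rho)/2

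| rho | adjusted vs follow-up only | sample-size equivalent | adjusted vs change | sample-size equivalent |
|---|---|---|---|---|
| 0.3 | 0.91 | 1.10 | 0.65 | 1.54 |
| 0.5 | 0.75 | 1.33 | 0.75 | 1.33 |
| 0.7 | 0.51 | 1.96 | 0.85 | 1.18 |

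Against follow-up only, 226 per arm is worth 226/0.75 = 301 at rho 0.5 and 226/0.51 = 443 at rho 0.7.

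**Effect of the trigger.** I simulated 20,000 trials per setting, taking a baseline difference at p<0.05 as the trigger. That threshold is an assumption, since the article gives none. Power is for an assumed true difference of 0.25 SD.

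| rho | power: never adjust | power: adjust if triggered | power: always adjust | type I error: adjust if triggered | type I error: better of the two p-values |
|---|---|---|---|---|---|
| 0.3 | 0.75 | 0.76 | 0.79 | 0.045 | 0.061 |
| 0.5 | 0.76 | 0.77 | 0.87 | 0.045 | 0.076 |
| 0.7 | 0.75 | 0.78 | 0.96 | 0.036 | 0.081 |

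A fixed trigger recovers little of the available power and is conservative. Inflation appears only if someone picks the more favourable of the adjusted and unadjusted results.

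**The case against.** The strongest reply is that the two sections fit together: the Secondary outcomes section names the comparison, and the Missing data section names MMRM as its form when visits are missed. That reading is reasonable. But the article never makes the link, and it does not say whether the MMRM conditions on baseline. The request for one named model therefore stands.

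A second reply is that trends over time may already treat baseline as a time point, and that the conditional ANCOVA may concern other factors, such as the NYHA class or diabetes listed for the primary analysis. This also has force. It moves the comparator from follow-up only to a change-type contrast, where the gain is 25% at rho 0.5 and 15% at rho 0.7. The factor of about 2.0 then no longer applies, but a gain remains at every correlation below 1.

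A reader might infer more than the article supports:
- **That the ANOVA drops anyone with a missed visit.** The article does not say so, and its commitment to ITT, MMRM and multiple imputation points the other way.
- **That conditional adjustment inflates type I error.** A fixed rule does not. Inflation needs a choice between results, which the wording permits but does not propose.
- **That follow-up LV function comes only from clinically driven imaging, by different modalities in the two arms, so that missing at random fails.** The Follow-up section does say "Clinical outcomes will be collected by telephone follow-up, and/or by hospital chart and electronic health record review". However, Secondary outcome measures says that "left ventricular function, QoL, referral to HF clinic, costs and safety will be assessed at three months" and then annually, and a condensed article may leave the imaging schedule to the full protocol. None of these steps is shown.

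**Conclusion.** The point holds for the repeated continuous secondary outcomes, chiefly MLHFQ and EQ5D. The article states two methods without ranking them, and it ties adjustment to an imbalance it does not define. This is a conflict in stated text, not detail left to an analysis plan.

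The size rests on an assumed correlation. At 0.5 to 0.7, always adjusting is worth about 1.2 to 2.0 times the sample size; the upper end holds only against a follow-up-only comparison. At 0.3 the variance saving against follow-up only is 9%. The selection risk, a type I error of roughly 0.06 to 0.08 across rho 0.3 to 0.7, is conditional on someone using the freedom that the wording leaves.

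The primary chi-square test and the 252 per group are not affected. The change is worth making because it is nearly free.

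**What to change.** Replace the ANOVA and conditional ANCOVA sentences under Secondary outcomes with one model: an MMRM in the ITT population with arm, visit, arm-by-visit and the baseline value of the outcome, always included. Name the main contrast (visit or average over follow-up) in advance. Fix any further covariates by name, so that none depends on observed differences. Under Missing data, refer to this model and say where multiple imputation applies.

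For LV function, it is enough to state that follow-up values come from the same modality in both arms and to report by arm how many patients have one.

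The cost is wording in the protocol, carried into the analysis plan; if that plan already names one model, the article's text need only be aligned with it. No new data, visits or patients are needed. The one added detail is a rule for patients without a baseline value.

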#### Economic evaluation

A cost minimization analysis comparing routine CMR versus standard care (echocardiography plus selective CMR) will be conducted. Analysis will be restricted to the follow-up period within the study database and will be conducted from the health care system perspective. Regression analysis will provide 95% confidence intervals around the estimate of incremental costs. In addition, univariate sensitivity analysis will be conducted to assess the robustness of the study’s results to changing assumptions related to the unit costs of specific resource items.

#### Safety analysis

Safety will be evaluated by documenting all adverse events. Descriptive statistics (frequency distributions, numerical descriptors) and 95% confidence intervals will be calculated. The As-treated population will be the main analysis population for this safety evaluation.

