#### Analysis populations

For the purposes of data analysis, three study populations will be considered: Intent-to-treat (ITT) population, As-treated population and Per-protocol population. The ITT population will be used for the main analysis for all primary and secondary objectives, except for the safety analysis where the As-treated population will be used. As a secondary analysis, the analyses will be repeated for the As-treated and Per-protocol populations.

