### Limitations

Given that CMR provides insight into myocardial characterization, we expect that the etiology of heart failure will be better characterized in those HF patients undergoing routine CMR. However, in some instances additional investigations such as myocardial biopsy and invasive hemodynamics may be required to confirm CMR findings. Therefore, the final diagnosis of heart failure etiology may ultimately be determined by CMR driven ancillary testing. We will assess the impact of downstream resource utilization on diagnosis and outcome in the multivariable analysis as well as calculate the additional cost burden.

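### As-treated is the main population for all adverse events, and no comparison by randomised arm is named for those other than death and heart failure admission

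*Protocol article*

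**What the plan says.** All references are to the protocol article.

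- **Population.** *Analysis populations* makes ITT the main population for the primary and secondary objectives, "except for the safety analysis where the As-treated population will be used". *Safety analysis* repeats the choice: "The As-treated population will be the main analysis population for this safety evaluation". As a secondary step, "the analyses will be repeated for the As-treated and Per-protocol populations". No ITT version of the safety analysis is named in either section.
- **Scope.** "Safety will be evaluated by documenting all adverse events", with descriptive statistics and 95% confidence intervals. *Secondary outcome measures* adds that "costs and safety will be assessed at three months, then annually for a minimum of one year and a maximum of four years".
- **Stated safety aim.** *Secondary objectives* is narrower: "Ancillary measurements will include the safety of imaging tests and adverse reactions to gadolinium contrast agent".
- **Downstream care.** *Limitations* expects that biopsy or invasive hemodynamics may be needed to confirm CMR findings, so that "the final diagnosis of heart failure etiology may ultimately be determined by CMR driven ancillary testing". *Secondary outcome measures* records disease-specific therapies at each follow-up.
- **By-arm clinical events.** The composite clinical endpoint ("death, cardiovascular (CV) death, HF admission") is compared between imaging strategies under *Secondary outcomes*, in the ITT population.
- **Crossover by design.** *Design* lets selective-arm patients have CMR when one of four named groups of conditions is suspected or uncertain. No expected rate is given.

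**The concern.** One population has to serve two kinds of event. A reaction to the scan or the contrast agent can occur only in a scanned patient, so a denominator of scanned patients is right. A complication of a later biopsy, or of a therapy started because of a CMR finding, is a consequence of the decision to image. Over a follow-up of up to four years such events can be part of all adverse events.

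The trial asks whether routine CMR should replace selective CMR, and the *Discussion* undertakes to judge the feasibility of a routine approach on safety as well as cost. For that, the reader needs adverse events per patient assigned to each strategy. Grouping by scan received gives a different contrast, scanned against unscanned. It is also confounded by indication, because selective-arm patients reach CMR through clinical suspicion.

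**Working it through.** **Plan's own figures.** The article gives none for safety. The 252 per group used below comes from *Sample size justification*. It is reproduced closely: 35% versus 50%, pooled-variance Z-test, power 90%, alpha 0.05 (two-sided assumed) gives 227 per group. Allowing for 10% loss gives 227/0.9 = 253 or 227 × 1.1 = 250.

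**Assumptions (none is in the documents).** Every routine-arm patient is scanned. Risk of an adverse event other than a scan or contrast reaction: u = 7% if unscanned, r = 10% in the routine arm, and c = 10% or 20% in selectively scanned patients. The value 20% represents a group selected for suspected disease. The share s of the selective arm that is scanned is 5%, 20% or 40%.

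**Formulas.**

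- By randomised arm: D_arm = r − [s·c + (1 − s)·u]
- By scan received: D_scan = (r + s·c)/(1 + s) − u
- Distortion: D_scan − D_arm = s(c − r)/(1 + s) + s(c − u)

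**Worked example, s = 20%, c = 20%.**

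- D_arm = 10 − (0.2 × 20 + 0.8 × 7) = 10 − 9.6 = 0.40 points
- D_scan = (10 + 0.2 × 20)/1.2 − 7 = 11.67 − 7 = 4.67 points
- Distortion = 4.67 − 0.40 = 4.27 points

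| s | Scanned / unscanned | c | By arm | By scan | Distortion |
|---|---|---|---|---|---|
| 5% | 265 / 239 | 10% | 2.85 | 3.00 | 0.15 |
| 5% | 265 / 239 | 20% | 2.35 | 3.48 | 1.13 |
| 20% | 302 / 202 | 10% | 2.40 | 3.00 | 0.60 |
| 20% | 302 / 202 | 20% | 0.40 | 4.67 | 4.27 |
| 40% | 353 / 151 | 10% | 1.80 | 3.00 | 1.20 |
| 40% | 353 / 151 | 20% | −2.20 | 5.86 | 8.06 |

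Differences are in percentage points.

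**Reading the table.** With c = 10% the selectively scanned patients carry the same risk as the routine arm. The two contrasts still differ, because scanned versus unscanned is not routine versus selective. With c = 20%, selection by indication enlarges the gap. The by-arm difference is then 3 − 13s points. It reaches zero at s = 3/13 = 23%, so above that share the two analyses point in opposite directions.

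**Alternative definition.** If As-treated means strategy received, a selective-arm patient scanned under the permitted indications stays in the selective group. With all routine-arm patients scanned, the As-treated and ITT groups coincide and the distortion is zero.

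**The case against.** The strongest reply has four parts.

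1. **As-treated is conventional for safety, and the named targets are imaging and contrast.** This stands for those targets. The article does not describe biopsy, invasive hemodynamics or disease-specific therapy as harms. They appear as diagnostic, cost and treatment matters, and that they can cause complications is an inference. But the same rule is applied to all adverse events over years, which is wider than the stated aim.

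2. **Strategy harm is estimated.** A reader might infer that no harm of the randomised strategy is ever estimated. The documents do not support that. Death, cardiovascular death and heart failure admission are compared by strategy under ITT, and calling As-treated the main population does not exclude a supporting one. What remains is that no by-arm summary is named for the other adverse events.

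3. **As-treated may mean strategy received.** This is open. The stated safety aim, and the descriptive summaries by imaging technology under *Statistical analysis*, lean towards scan received. Repeating the routine-versus-selective comparisons in the As-treated population leans the other way. The concern therefore has to be conditional.

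4. **The safety analysis is descriptive, and every risk used here is assumed.** Both are true. No between-group test is stated, so the distortion would arise when a reader sets the two columns side by side. A reader might also infer that the apparent harm of routine CMR would be multiplied by some fixed factor. No such factor can be claimed, since the selective-arm scan rate is not given and the gap is slight when that rate is low.

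An unseen analysis plan might add the table. The population is nevertheless fixed in the article, so this concerns a stated rule and not an omitted detail.

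**Conclusion.** The point holds in a limited form. As-treated is right for scan and contrast reactions. For the remaining adverse events the article names no comparison by randomised arm. If As-treated means scan received, its grouping cannot give the effect of choosing routine over selective CMR.

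On the assumed risks, the distortion runs from 0.15 points (5% selective-arm use, equal risk in scanned patients) to about 8 points (40% use, doubled risk in those selectively scanned). It is nil under the strategy-received definition. The result rests on the assumed risks, full scanning of the routine arm and an unstated selective scan rate. Safety is an ancillary, descriptive objective, so importance is modest. The change is still worth making, because it removes a selection bias under one definition and does no harm under the other.

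**What to change.** Amend *Analysis populations* and *Safety analysis* to split the evaluation:

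- **Imaging and gadolinium reactions:** keep As-treated, summarised in all scanned patients from either arm.
- **All other adverse events**, including complications of downstream testing and of disease-specific therapy: summarise by randomised arm (ITT) with 95% confidence intervals.

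A short clause saying whether As-treated refers to the scan or the strategy received would settle the ambiguity. The cost is this wording and one more table. No new data are needed, since all adverse events are already to be documented.
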